### Monitoring

#### Data Monitoring

A data monitoring committee will not be needed as this will be a minimal risk trial.

#### Risks Related to the Intervention

Physical discomfort caused by the weight of the VR headset or simulation sickness may arise with extended VR use. Muscle soreness because of repetitive use of muscle groups may occur, and skin irritation from adhesives is possible. There is a risk of seizure using the VR headset estimated to be 1 in 4000 in the general population.

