## Abstract

**Background:**

Cerebral palsy (CP) is the most common developmental motor disorder in children. Individuals with CP demonstrate abnormal muscle tone and motor control. Within the population of children with CP, between 4% and 17% present dystonic symptoms that may manifest as large errors in movement tasks, high variability in movement trajectories, and undesired movements at rest. These symptoms of dystonia typically worsen with physical intervention exercises.

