## Introduction

### Background

Cerebral palsy (CP) is the most common developmental motor disorder in children, present in 3.6 of every 1000 live births in the United States [1]. Individuals with CP demonstrate abnormal muscle tone and motor control that contribute to impaired postural control and movement coordination that compromise health [2,3]. CP is considered a static encephalopathy; there is no known cure, and the physical impairments present at early age tend to worsen with time [4].

Between 4% and 17% of children with CP present dystonic symptoms as the predominant motor impairment [5]. Dystonia is typically characterized by involuntary muscle activity that may be sustained or intermittent, thereby causing abnormal postures or movements that can be described as trembling, writhing, or contouring [6-8]. These abnormal movements are often present during attempted voluntary movement and can worsen when this movement is sustained [7].

Approximately 70% of children with CP present spastic symptoms. Spasticity manifests as (1) increased resistance to external muscle stretch that varies with flexion or extension and/or (2) resistance that quickly rises past a certain joint angle position or velocity [6,7]. Dystonia and spasticity often manifest in the same child with CP [5,7,9].

The main goals of rehabilitation in CP include promoting function while decreasing the risk for skeletal deformity and muscular atrophy later in life [10-14]. Rehabilitative therapies for CP most commonly include orthopedic surgery, botulinum toxin injections, and physical therapy (PT). PT interventions consist of intensive stretching and strengthening exercises and, more recently, high dosage robotic training [10-14]. However, dystonia worsens with PT and is often “refractory to treatment” [15]. Management of dystonia typically involves oral medication that produces little improvement and may have adverse side effects [16]. It has been recently shown that deep brain stimulation provides only moderate benefits in some patients with dystonia and none in others [16-21]. In individuals with combined spasticity and dystonia, physical interventions that improve spastic symptoms cause worsening of dystonic symptoms [7].

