### Outcomes

All participants will be assessed for outcome measures at a site using sEMG sensors embedded with inertial measurement units (ATI-Nano 25, ATI Industrial Automation, North Carolina) and the robot-force transducer unit. All assessments and measurements are noninvasive and involve minimum risk to the participants. The accelerometry data will be used to assess smoothness of movement during the execution of a prescribed movement and measures muscle activation patterns during assessments involving the robot-force transducer unit used to measure force and torque outputs within the reachable space of the upper limbs of the participant. In addition, the robot is programmed to produce a path of zero resistance, within the reachable space, that provides haptic feedback perpendicular to the path. For assessing children with CP, we will collect clinical and quantitative measures of upper limb range of motion, motor function, dystonia, and spasticity. The outcome measures will be obtained before, after the intervention, and at 1-month follow-up (Textbox 2).

Assessments 1 to 4 are standard clinical questionnaires and tests. Assessment 5 is a quantitative test of spasticity based on sEMG recordings and angle velocity of a joint by manual manipulation.

Assessment 6 involves the robot, force sensor, and sEMG. A predetermined zero-force path has been programmed by the research team to allow the robot to move through straight lines connected to 5 points on a vertical plane. These positions coincide with the 5 positions of the training intervention, resting in a reachable rhombus-like configuration. The participants will attempt to find and move along a zero-force path. The force transducer will measure the forces exerted by the participant as they do so. This task will be limited to a 7-min period or until the task is complete.

Measured outcomes. Measures for all participants (ie, listed from 6 to 10 will be done for all participants). The remaining articles are outcome measures for participants with cerebral palsy, that is, these will be specific to participants with cerebral palsy.Dyskinesia Impairment ScaleSelective Control of the Upper Extremity ScaleQuality of Upper Extremity Skills TestTardieu TestMontreal Spasticity Rating TestZero-Force Channel AssessmentSurface electromyography and accelerometryForces and torques against force sensorWorld Health Organization Disability Assessment Schedule 2 Children and YouthQualitative Feedback Module

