### Blinding

Research team members administering clinical assessments will be blinded from participant allocation. Participant’s allocation will not be revealed during the course of the study.

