#### Safety Measures

To avoid simulation sickness, the programed VR images are slow, soothing, and were created following Oculus Best Practices Version 310-30000-02 as provided by Oculus VR, LLC. In addition, any health risks associated with VR headset use in children will be mitigated by referencing the Health and Safety Warnings provided by Oculus VR, LLC; children younger than 13 years will not be permitted to use the virtual headset. The participant has the option to play the game on a flat monitor or using a VR headset according to their preference. If simulation sickness arises, no medication will be administered as it is not a severe side effect of VR. Grounding exercises may be done if needed or the participant may decide to stop for the day or continue without the headset. Headset use will be limited to 30-min intervals.

Aside from maximum voluntary efforts, most efforts that participants produce will be 30% ± 10% of their maximum voluntary effort. The experiment will also be conducted in a seated position, reducing risk of injury because of falls, and ample care will be taken to ensure the participants’ comfort as needed including provision of seat cushions. Trained research personnel will use gait belts, when needed, to transport participants from their wheelchair to the chair used for the experiment and back to their wheelchair as necessary. If their wheelchair allows for interaction with the robot, no transfer will take place. Surfaces that come in contact with participants are wiped down with hospital grade antiviral and antibacterial wipes before and after use.

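### The article treats worsening dystonia as a usual effect of physical intervention, yet omits it from its risk list and safety responses and next rates dystonia only after all six training sessions

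*Protocol article*

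**What the plan says.** **On the hazard.** The Abstract says of dystonia: "These symptoms of dystonia typically worsen with physical intervention exercises". The Background repeats the point for physical therapy and adds of the abnormal movements: "These abnormal movements are often present during attempted voluntary movement and can worsen when this movement is sustained". It then gives the reason for the design: a low-magnitude isometric task, meant to limit the noise mechanism thought to cause the worsening.

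**On risk.** Risks Related to the Intervention names discomfort from the headset, simulation sickness and seizure, and states: "Muscle soreness because of repetitive use of muscle groups may occur, and skin irritation from adhesives is possible". Safety Measures mentions the force level, "Aside from maximum voluntary efforts, most efforts that participants produce will be 30% ± 10% of their maximum voluntary effort", without linking it to dystonia. Data Monitoring states: "A data monitoring committee will not be needed as this will be a minimal risk trial". Harms is a single sentence on communication with the two institutional review boards.

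**On measurement.** The DIS is the dystonia scale, used in CP participants. Outcomes states: "The outcome measures will be obtained before, after the intervention, and at 1-month follow-up". Choice of Comparator puts controls on the same assessment schedule. Blinding states: "Research team members administering clinical assessments will be blinded from participant allocation".

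**On analysis.** Statistical Methods plans paired tests within the CP and typically developing groups. Secondary outcomes are exploratory, and missing values may be omitted or corrected for.

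**The concern.** The article builds its rationale on one disease-specific hazard, then writes its risk and safety sections as if that hazard did not exist. If the low-force design does not prevent worsening in some children, three things follow from the text as it stands:

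- no scheduled step looks for worsening while training is still going on;
- worsening that resolves before the post-assessment leaves no planned record;
- a child who stops early, possibly because of worsening, may contribute no later dystonia score, and missing values may then be dropped.

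At stake are the safety of the trained CP children and the ability of a pilot trial to say how many of them got worse.

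**Working it through.** **1. Set the risk and safety text against the rationale.** The inputs are Background, Risks Related to the Intervention and Safety Measures.

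| Hazard | In the risk list? | Precaution or response described? |
|---|---|---|
| Headset discomfort | Yes | Yes: monitor option, time limit |
| Simulation sickness | Yes | Yes |
| Seizure | Yes | Yes, an eight-point procedure |
| Skin irritation | Yes | Allergy is an eligibility bar |
| Muscle soreness | Yes | Mostly low efforts |
| Falls and transfers | No | Yes: seated position, gait belts |
| Robot or power fault | No | Yes |
| Worsening dystonia | No | None named |

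The last row is the only hazard that the article itself describes as usual with physical intervention in this population.

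**2. Is the low-force task already shown to avoid it?** The Background states its effect as a hypothesis, and Comparison With Prior Work reports none completed. Limitations cites a similar study with improvements over the same number of sessions, but in spasticity. The Background says that physical interventions which help spasticity make dystonia worse when the two coexist. The mitigation is reasoned but untested here.

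**3. Place the DIS on the calendar.** Count Saturday of week 1 as day 1.

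| | Baseline | Training sessions | Post-assessment |
|---|---|---|---|
| Table 3 | days 1–2 | days 3, 5, 7, 10, 12, 14 | days 15–16 |
| Table 4 | days 1–2 | days 3, 4, 5, 6, 7, 8 | days 9–10 |

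Six of six sessions fall between consecutive ratings in both schedules. Assessments may move by up to a week, which changes the gap but not the order. The only outcome recording described within the training window is electromyography and accelerometry on the first and last game day, and neither is a dystonia rating.

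**4. What can be counted from the planned data?** The article's attrition figure reproduces: 17 × (1 − 0.25) = 12.75, about 13 per group. The documents give no rate of worsening, so the rates below are assumptions. The chance of seeing at least one worsened child among n trained CP children is 1 − (1 − p)^n.

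| Assumed rate p | n = 17 | n = 13 |
|---|---|---|
| 5% | 0.58 | 0.49 |
| 10% | 0.83 | 0.75 |
| 20% | 0.98 | 0.95 |

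If no child worsened, the one-sided 95% upper limit, 1 − 0.05^(1/n), would still be 16% (n = 17) or 21% (n = 13). A two-sided paired t test at 0.05 has 80% power only for a mean worsening of about 0.72 (n = 17) or 0.85 (n = 13) standard deviations of the change. Lasting worsening in completers is therefore countable, though imprecisely. A count of individuals by arm shows what a test of the mean could miss.

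**The case against.** The strongest reply is that the article gives a rationale followed by a mitigation. The Background describes conventional therapy as intensive stretching, strengthening and high-dosage robotic training, and then chooses a different, low-force task. No statement predicts that this intervention worsens dystonia. That stands, so the point is an omitted potential risk and not an admitted one. Maximal efforts do not change this much. They belong mainly to assessments, which both arms undergo, and enter training sessions only when electromyography is used.

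A reader might infer that worsening could be neither noticed nor counted. The documents do not support that. The DIS is taken at baseline, post-assessment and 1 month in randomised CP controls as well, with clinical assessors blinded, and the Abstract promises to report negative results. A trained researcher is beside the child, a guardian is asked to be present, sessions are filmed, and a child may rest between efforts or stop at any time. These allow informal detection, but none is a scheduled check for dystonia.

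A reader might also turn the 25% attrition into about four of 17 trained CP children (17 × 0.25 = 4.25) without a later DIS. The article gives neither cause nor timing for attrition, so this is at most a ceiling. Nor does it say that only means will be reported, or plan any tolerability conclusion that could be biased.

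Finally, adverse-event definitions and review procedures often sit in a full protocol, and the consent form is not shown. That rules out claiming that no response exists anywhere. It does not excuse the inconsistency, because the article has its own risk and safety sections, detailed down to seat cushions and disinfectant wipes.

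**Conclusion.** The point holds as an internal inconsistency with a measurement gap, and should be corrected before enrolment. The article describes worsening dystonia as usual with physical intervention, offers an untested mitigation, and then leaves the hazard out of its risk list and safety responses while calling the trial minimal risk. All six sessions precede the next dystonia rating. Lasting worsening in completers is captured in both CP arms. Earlier or transient worsening depends on informal observation, and no DIS is described for early leavers.

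The conclusion rests on the article alone and on the two example schedules. How often worsening would occur is unknown, and the rates used above are illustrations.

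**What to change.** 1. Reconcile the Abstract and Background with the sections from Data Monitoring to Harms, and name worsening of dystonia as a potential risk in Risks Related to the Intervention.
2. Add one fixed question on worsening, put to the guardian or child, to the existing procedural checklist before each training session for CP participants. Pass the answers to the investigator and keep them from the blinded assessors. The question is for detection: only trained children are asked, so it gives no comparison between arms.
3. Obtain a DIS from any CP child who stops early and is willing.
4. Report the number of CP children with a DIS worse than baseline by randomised arm, with the number lacking a later score. The control count shows how much apparent worsening arises without training, including from measurement error.

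Any threshold, or any action on training, is for the investigators to set. The cost is a few lines of text, about a minute per session, and occasionally one existing scale at exit. The trial had not started when the article was written.

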#### Safety Measures

To avoid simulation sickness, the programed VR images are slow, soothing, and were created following Oculus Best Practices Version 310-30000-02 as provided by Oculus VR, LLC. In addition, any health risks associated with VR headset use in children will be mitigated by referencing the Health and Safety Warnings provided by Oculus VR, LLC; children younger than 13 years will not be permitted to use the virtual headset. The participant has the option to play the game on a flat monitor or using a VR headset according to their preference. If simulation sickness arises, no medication will be administered as it is not a severe side effect of VR. Grounding exercises may be done if needed or the participant may decide to stop for the day or continue without the headset. Headset use will be limited to 30-min intervals.

Aside from maximum voluntary efforts, most efforts that participants produce will be 30% ± 10% of their maximum voluntary effort. The experiment will also be conducted in a seated position, reducing risk of injury because of falls, and ample care will be taken to ensure the participants’ comfort as needed including provision of seat cushions. Trained research personnel will use gait belts, when needed, to transport participants from their wheelchair to the chair used for the experiment and back to their wheelchair as necessary. If their wheelchair allows for interaction with the robot, no transfer will take place. Surfaces that come in contact with participants are wiped down with hospital grade antiviral and antibacterial wipes before and after use.

Potential participants with a history of seizures will not be included in the study. Research personnel are trained to manage the rare event of a first seizure and follow the guidelines of the British Epilepsy Association: (1) remove objects nearby and cushion the head, (2) note the time when jerking starts, (3) place the person on one side of their body in recovery position after any jerking stops, and (4) stay with the person. In addition, (5) movement will not be restrained, (6) no objects will be put in the mouth, (7) the person will not be moved, and (8) no food or drink will be given until full recovery [35]. If the person is seated in a wheelchair, the brakes will be put on, and the person will be gently supported to prevent falling out of the chair if necessary. Research personnel will call for an ambulance, as it would be the person’s first seizure. The experiment will be stopped, and the participants’ guardian will be advised to seek immediate medical attention. The guardian will be asked to stay present during each session. If a seizure were to occur, the participant will not be allowed to continue with the study as the inclusion and exclusion criteria will no longer be met.

The robot (KUKA Roboter gmbh, Augsburg, Germany) is approved for human-robot collaborative mode and is assured to perform as instructed. A trained researcher will be next to the participant and robot at all times and will be prepared to unplug the robot if any unexpected movement of the robot occurs. The participant is not secured to the robot as well, which allows the participant to release the end effector if necessary. In addition, if a large force is applied to the robot, the uppermost link will turn off. The gripper mounted on the sensing surface of the force and torque transducer is rounded with no sharp edges.

Additional safeguards are included in the inclusion and exclusion criteria, in the consent and assent forms, and in the protocol design. In addition, the assent forms have extensive language describing the study and allow for the termination of participation by the participant at any time and for any reason.

We have tested the system extensively and do not expect any major changes or bugs. In case of any unexpected event, including situations of power failure in which testing has proven to cause no harm to the participant, the experiment will be stopped, and the research team will test the system to ensure functionality. Participants will be asked to return to the site on another day and will be reimbursed for the additional time.

#### Benefits

The participants may not receive any direct benefit beyond the satisfaction of participating in research, playing a VR game, and advancing the knowledge of motor control and coordination in humans. However, participants may notice improved control of movement of the upper limbs. The benefit to society rests on the advancement of our understanding of motor control and coordination in humans as well as improving diagnostic specificity in CP and providing a possible therapy modality. This information may be used to train future physicians.

#### Harms

All communications will be sent to both the Peoria and UIUC institutional review boards (IRBs).

#### Auditing

Auditing will be done as per the policies of the sponsor and the bodies that have sponsor oversight.

#### Ethics and Dissemination

Approval from the study sites institutional review boards will be sought. All protocol modifications will be communicated to both IRBs.

Potential participants and a parent or guardian will have the option to sign an assent and consent form, respectively, for participation in the study.

Identifiable elements including names, phone numbers, street addresses, city or state, zip code, email addresses, date of birth, grade level in school, and photos and videos (no close-up footage) will be collected. Screening materials will be kept for the participants that enroll in the study and destroyed for those that do not meet the criteria or decide not to enroll. Authorization for use and disclosure of the participants’ personal health information for this specific study does not expire. The data will be kept for 5 years after publication, as required by the American Psychological Association. Identifiers will be destroyed 5 years after the completion of the study.

Personal contact information will be used for the study team to contact participants during the study. Health information and results of tests and procedures are being collected as part of this research study for fulfillment of inclusion criteria and for the advancement of clinical care. By signing assent and consent forms, permission is given to the principal investigator and the research team to use the protected health information for the purposes of the study. Permission is also granted to the OSF Healthcare System and the University of Illinois College of Medicine at Peoria to disclose or release the participants’ protected health information for this study.

If suspected abuse, neglect, or exploitation of a child or a disabled or elderly adult is disclosed, the researcher or members of the study staff will report the information to Child Protective Services, Adult Protective Services, or a law enforcement agency.

Images and videos will be stored without personal identifiers associated with the files apart from the image or video itself. If permission is given, these photos could be included in scholarly publications in print and electronic form, which will allow participants’ faces to potentially be visible and recognizable by anyone reading the publications. Photos and videos may also be presented at meetings or conferences without any personal identifiers attached to the photos and videos other than the content itself. Data will be kept with coding and will only be viewable by lab personnel who are associated directly with the maintenance of data for this study.

Video footage with audio will be recorded at all sessions to ensure safety and adhesion to study protocols as well as to record the study. The footage is being taken to ensure the rights of participants and for the researchers alike. By signing the consent and assent forms, authorization is given for the principal investigator and research team to record the participant during participation of the study and to share the footage with the following items if emergencies arise or the research protocol is not properly followed:

The IRBsThe Office of Human Research OversightAuthorized members of the University of Illinois College of Medicine Peoria workforceRepresentatives of the university committee and office that reviews and approves research studiesOffice for Protection of Research SubjectsOther representatives of the state and university responsible for ethical, regulatory, or financial oversight of researchFederal government regulatory agencies such as the Office of Human Research Protections in the Department of Health and Human Services

